** *Community-level Characteristics* **		
Access	Distances to the nearest Medicaid MOUD prescriber and other addiction treatment programs; low threshold buprenorphine programs; harm reduction providers or drug user health hubs providing MOUD services	Medicaid
Community Resources	Social vulnerability index (SVI) (i.e., composite measure of area-level vulnerability to adverse outcomes); racial/ethnic composition of community; population density; density of OUD among Medicaid members; proportion of Medicaid OUD members receiving MOUD	Census Medicaid
** *Outcome Variables* **		
MOUD Use*	Claim for methadone, buprenorphine (including formulation, e.g., sublingual tablets, sublingual film, subcutaneous injection, and implants), XR naltrexone	Medicaid
Adherence to MOUD*	Continued receipt of MOUD (continued methadone program appointments or renewal of buprenorphine or naltrexone prescriptions)	Medicaid
Retention*	Length of stay in treatment episode (in days)	Medicaid
Adverse Event*	SUD-related emergency department visit or hospitalization, including for overdose; increase in SUD level of care	Medicaid
Healthcare Utilization*	All-cause emergency department visits and hospitalizations	Medicaid

Table Notes: OASAS = CDS database; * Time-varying variables

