#### Aim 3. Examine the association between program organizational characteristics and adverse OUD-related events (AE) such as overdose, while accounting for individual and community factors

Our third aim centers on investigating the nexus between program organizational characteristics and OUD-related adverse events among TA adults including SUD-related emergency department visits or hospitalizations, including for overdoses, and increases in levels of SUD care. We will examine the association between program structural factors (e.g., program size and type) and AE outcomes. Additionally, we will examine how program staff characteristics (e.g., professional degrees) impact AE. We also will explore the association between clinical care process measures (e.g., use of telehealth, counseling modalities) and AE outcomes.

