### Analysis

The study uses rigorous methods to address questions about multilevel factors associated with MOUD use, retention, and adverse event mitigation. Table 1 below outlines measures aligned with the social ecology framework and data sources. Baseline patient, program, and community characteristics will be assessed at admission, while ongoing treatment and healthcare measures will be assessed monthly. We also will compare pre- and post-COVID-19 treatment patterns to examine care innovations on retention and outcomes, like telehealth and flexibility in methadone take-home doses. We present an outline of the analytical approach, specifying the strategies we intend to employ for each of our three aims.

**Table 1 pone.0297567.t001:** Summary of outcome and predictor variables and sources by level.

Concept	Variables	Source

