** *Treatment Program Organizational Characteristics* **		
Structure	Specialty opioid treatment program; program size (i.e., annual patient volume); % of TA adults among all clients; % OUD among clients; type (i.e., inpatient, outpatient); hospital system affiliation; integrated license for mental health services	OASAS Medicaid
Staffing	Number of staff; staff professionalization (e.g., degrees); gender and race/ethnicity; client-to-staff ratio	OASAS
Clinical Process	% MOUD (e.g., methadone, buprenorphine, XR naltrexone) among OUD clients; average monthly volume claims for individual, group, peer, and family counseling; average monthly volume claims for telehealth use; monthly volume for toxicology screening	Medicaid

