#### Aim 3: Examining program characteristics and adverse OUD-related events

Our final objective is to examine the association between treatment program organizational characteristics and adverse OUD-related events (AE) such as an SUD-related emergency department visit, including for overdose, while accounting for individual and community characteristics. Like Aim 2, we will employ time-to-event methods, focusing on the occurrence of the first adverse event. The adjusted hazard ratio of program structural factors, staff characteristics, and clinical care delivery features will be evaluated against a null hypothesis of 1. We will conduct sensitivity analyses akin to those described in Aim 2, ensuring the robustness of our results and conclusions. Applying the Lachin-Foulkes method to a study spanning 14 years, with variable drop-out rates, we determined that our sample size (>65,000) provides substantial power to detect clinically significant associations. Even under variable rates of attrition (10%-70%), we maintain adequate power to detect hazard ratios of 1.15 (or 0.87) with 80% power and a 5% type I error rate. Given the estimated study sample (>65,000), we are powered adequately to detect clinically meaningful associations.

*Aim 3a*: *Program structural factors and AE*. First, we will investigate the relationship between program structural elements (e.g., program size and type) and the occurrence of adverse OUD-related events (AE).

*Aim 3b*: *Program staff characteristics and AE*. Second, we will explore the connection between program staff attributes (e.g., professional degrees) and the incidence of adverse OUD-related events.

*Aim 3c*: *Clinical care process measures and AE*. Third, we will assess how clinical care processes (e.g., use of telehealth, counseling modalities) are associated with the prevalence of adverse OUD-related events.

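### Aim 3a compares inpatient with outpatient programs on a first-event composite that includes a step-up in care, which patients at the highest level cannot have until they step down

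*Protocol article*

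**What the plan says.** - **Endpoint.** The Adverse Event row of Table 1 (Outcome Variables) reads "SUD-related emergency department visit or hospitalization, including for overdose; increase in SUD level of care". The statement of Aim 3 under Study design and aims says the same: "including SUD-related emergency department visits or hospitalizations, including for overdoses, and increases in levels of SUD care". The step-up component is therefore not a stray table entry.
- **First event.** The Aim 3 part of the Analysis section states: "Like Aim 2, we will employ time-to-event methods, focusing on the occurrence of the first adverse event".
- **Exposure.** Aim 3a names program size and type. The Structure row of Table 1 defines the latter as "type (i.e., inpatient, outpatient" and so on, which is itself a level of care. The Analysis section adds: "Baseline patient, program, and community characteristics will be assessed at admission".
- **Test.** "The adjusted hazard ratio of program structural factors, staff characteristics, and clinical care delivery features will be evaluated against a null hypothesis of 1".
- **Sensitivity analyses.** Aim 3 takes over those of Aim 2: plausible instruments for program selection and mixed-effects Cox models.

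The article does not limit the risk set to patients who can still move up, does not stratify the component by starting level, and describes no model for the acute events alone.

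**The concern.** The exposure is a level of care, and one component of the endpoint is a move to a higher level. While a patient is at the top level, that component cannot occur; an outpatient is at risk of it from the first day. Exposure and outcome are linked by definition, not by confounding. Adding covariates does not break the link. The borrowed sensitivity analyses do not break it either: they address program selection and clustering, and a valid instrument would still estimate an effect on the same composite.

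At stake is the reading of one Aim 3a result. A hazard ratio for program type away from 1 could be reported as a difference in harm when overdose, ED visits and hospitalizations do not differ.

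**Working it through.** **1. The plan's own figure.** Aim 3 states 80% power at 5% type I error for a hazard ratio of 1.15 (or 0.87) with more than 65,000 patients and 10%–70% attrition. By Schoenfeld's formula, assuming a two-sided test and a 1:1 split, the events needed are 4 × (1.960 + 0.842)² / (ln HR)². This gives 1,608 for 1.15 and 1,619 for 0.87. The first is 1,608 / 65,000 = 2.5% of the cohort, or 1,608 / 19,500 = 8.2% of those left after 70% attrition. The claim is plausible but cannot be verified, because no event rate or exposure split is given. It serves here only as a yardstick.

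**2. Assumptions.** The article gives no rates, so all of these are assumed:
- acute events (SUD-related ED visit or hospitalization) have hazard *a* in both program types, so there is no true difference;
- step-up has hazard *u* in outpatients and zero in inpatients until they step down;
- inpatient is the top level;
- the time to step-down is exponential, with mean *m*.

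**3. No step-down.** The composite hazard ratio, inpatient versus outpatient, is a / (a + u) = 1 − s, where s = u / (a + u) is the share of outpatient first events that are step-ups.
- a = 0.20, u = 0.10 per year: 0.20 / 0.30 = 0.67.
- a = 0.20, u = 0.03 per year: 0.20 / 0.23 = 0.87, with s = 13%.

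**4. With step-down.** If q(t) is the proportion of still event-free inpatients who have stepped down by time t, then HR(t) = (a + u·q(t)) / (a + u). The Cox model averages this over the event times. Large-sample results:

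| a, u per year | Mean inpatient stay | 3 months | 1 year | 5 years |
|---|---|---|---|---|
| 0.20, 0.10 | never steps down | 0.67 | 0.67 | 0.67 |
| 0.20, 0.10 | 90 days | 0.79 | 0.91 | 0.97 |
| 0.20, 0.10 | 28 days | 0.90 | 0.97 | 0.99 |
| 0.20, 0.03 | never steps down | 0.87 | 0.87 | 0.87 |
| 0.20, 0.03 | 90 days | 0.92 | 0.97 | 0.99 |
| 0.20, 0.03 | 28 days | 0.96 | 0.99 | 1.00 |

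Hand check for 28 days at 1 year: m = 28/365 = 0.077. The mean of q is about 1 − 0.077 × (1 − e^(−1/0.077)) = 0.923. Then (0.20 + 0.10 × 0.923) / 0.30 = 0.97.

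**5. Change of sign.** Take a = 0.48 and u = 0.12 per year (s = 20%), a 28-day mean stay, and a step-up rate after step-down twice the outpatient rate. Simulation gives 1.16 at 1 year. The same hand check gives (0.48 + 0.24 × 0.923) / 0.60 = 1.17.

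**6. Effect on the test, and after the fix.** These come from Cox simulations with no true difference in acute events: 20,000 patients, 20% inpatient, total outpatient hazard 0.6/year, s = 20%, 1 year of follow-up. There were 100 runs per setting, and 400 for the last row.

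| Endpoint | Step-down | HR | Rejections at 5% |
|---|---|---|---|
| Composite | never | 0.80 | 100% |
| Composite | mean 90 days | 0.95 | 47% |
| Composite | mean 28 days | 0.98 | 12% |
| Acute events only | not relevant | 0.998 | 4.8% |

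**The case against.** **Long follow-up dilutes the bias.** The Sample section keeps each person in the dataset in all later years, and the Aim 3 power statement speaks of 14 years. Patients who step down become able to step up, and by 5 years the hazard ratio is near 1 in every step-down case in step 4. This stands. It rules out quoting 0.67 or 0.87 as the expected bias; those are the no-step-down bound.

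**The components may be separate outcomes.** In Table 1, semicolons elsewhere divide distinct variables. The aim statement speaks of outcomes in the plural, and the Aim 3 analysis text names only the ED visit as its example. This reading is possible but weaker than the plain wording "focusing on the occurrence of the first adverse event".

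**A broader outcome is already listed.** Table 1 includes all-cause ED visits and hospitalizations. That outcome has no ceiling, but it is not SUD-specific and no model is described for it.

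**Event construction belongs in the full plan.** Often so. Here, however, the article itself fixes the composite, the first-event rule and the exposure, and the problem is their combination.

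**Treating a step-up as adverse is a legitimate choice.** It can mark deterioration. This stands, and it is a reason to keep the component as an outcome of its own. Losing later events after the first is common to every first-event composite and is no special fault here.

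**Staffing and process exposures.** A reader might infer that programs which refer patients upward readily will look more harmful. The article does not support this as a finding. No figure bears on it, and the models enter program-level variables, so adjustment for type can absorb much of the ceiling. It is a possibility only.

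**Conclusion.** The point holds for program type in Aim 3a. The endpoint and the exposure are linked by definition, and nothing described in the article removes the link. It does not concern program size as such.

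Size and sign cannot be fixed, because the event rates, the share of step-ups, the split of patients by type and the length of inpatient stay are all absent. Under the assumed 0.20 and 0.10 per year, the hazard ratio with no true difference runs from 0.67 (no step-down) through 0.91 or 0.97 at 1 year to 0.97 or 0.99 at 5 years. With s = 20% and doubled step-up after a 28-day mean stay, it is 1.16 at 1 year.

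A reader might infer that a 13% share of step-ups would by itself produce the plan's detectable 0.87. That needs inpatients never to step down, or follow-up to end at or soon after inpatient discharge, and the article says neither. The working also takes inpatient as the top level. The article does not list the levels; if some inpatients can still move up, the bias is smaller.

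The limitations section's caution about causal inference concerns program selection and does not cover this. The plan should be changed, but the rest of Aim 3 does not fall with it.

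**What to change.** - **Endpoint for program type in Aim 3a.** Use the first SUD-related ED visit or hospitalization, including for overdose.
- **Definition of hospitalization.** State that admission to an SUD treatment program which is itself a level-of-care increase does not count. Otherwise the same link returns through this component.
- **Step-up.** Analyse an increase in SUD level of care as a separate outcome, restricted to or stratified by starting levels from which an increase is possible.

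The cost is somewhat fewer first events, plus the work of classifying each patient's starting level and building the restricted risk set. The Status section reports that no data analysis had been done, so on that account the definition could be changed before any result was seen.

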#### Aim 1: Quantifying associations between MOUD use and social and ecological factors

To quantify the associations between MOUD use (e.g., methadone, buprenorphine, XR naltrexone) and individual, community, and treatment program organizational characteristics, we will use generalized linear mixed effects models (GLMM). The primary outcome of interest is whether an individual received MOUD during the treatment episode. We will include random effects to account for repeated measurements within individuals and clustering by program and county, and time fixed effects to address secular trends, such as the pre- and post-COVID-19 periods. We will test whether models can be simplified by replacing time fixed effects with time-related splines or power terms. We also will explore interactions among variables of substantive interest (e.g., varying the effect of criminal justice involvement on OUD treatment by community influences and program organizational factors). We will adopt a generalized estimating equations approach with robust standard errors to ensure the robustness of our findings. To address potential bias associated with correlations between predictors and random effects, we will utilize the Mundalk approach of mean-centering variables within county. A penalization approach (lasso regression) will be used for feature selection to address overfitting and collinearity. The validity of the approach will be ensured using cross-validation and sample splitting. Given the large sample size (>65,000) across multiple years, we are powered to detect conservative odds ratios (≥1.1) with 80% power at a two-sided alpha of 0.05 (assuming 10% overall prevalence of MOUD use). Higher prevalence will lead to improved power.

*Aim 1a*: *Associations with psychological and social determinants of health*. First, we will explore the association between MOUD use and psychological and social determinants of health at both the individual (e.g., housing status, comorbid mental health diagnoses) and community levels (e.g., social vulnerability index, program availability). For each group of measures, we will build distinct GLMMs. These models will be adjusted for age, sex, race, as well as other individual baseline and time-varying covariates (as specified in the measures table).

*Aim 1b*: *Associations with program organizational characteristics*. Second, we will focus on examining the connection between MOUD use and treatment program organizational characteristics (e.g., program size and type, volume of telehealth, integrated mental health treatment). Like Aim 1a, we will use GLMMs to analyze treatment program measures. These models will be adjusted for age, sex, race, other individual and community baseline measures, and other time-varying covariates (as detailed in the measures table). For aims 1a and 1b, estimates of odds ratios and their corresponding 95% confidence intervals will be reported.

*Aim 1c*: *Associations with MOUD options*. Third, we will investigate the factors linked to the use of different MOUD options (e.g., buprenorphine, methadone, or XR naltrexone) at individual, program, and community levels. To explore the association between medication option, provider proximity, and racial/ethnic patient characteristics, we will employ mixed effects multinomial logistic regression, while adjusting for individual, program, and county level covariates.

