**Methods:**

We introduce a retrospective, longitudinal cohort design to study treatment quality practices and outcomes among approximately 65,000 TA adults entering treatment for OUD between 2012 and 2025 in New York. We propose to combine data from multiple sources, including Medicaid claims and encounter data and a state registry of substance use disorder (SUD) treatment episodes, to examine three aspects of OUD treatment quality: 1) MOUD use, including MOUD option (e.g., buprenorphine, methadone, or extended-release [XR] naltrexone); 2) adherence to pharmacotherapy and retention in treatment; and 3) adverse events (e.g., overdoses). Using rigorous analytical methods, we will provide insights into how variation in treatment practices and outcomes are structured more broadly by multilevel processes related to communities, treatment programs, and characteristics of the patient, as well as their complex interplay.

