### Study design and aims of the study

Our study introduces a retrospective, longitudinal cohort design to assess treatment quality practices and outcomes among TA patients with OUD in NYS using administrative data from 2010 through 2025. We will combine Medicaid claims and encounter data with data from the Client Data System (CDS), a state registry of treatment episodes in licensed SUD treatment programs. CDS is an Office of Addiction Services and Supports (OASAS) treatment registry that all licensed providers of SUD treatment in the state of New York use to enter admission and discharge data. Data include demographics (e.g., age, race/ethnicity, and marital status), level of functioning (e.g., housing status, health status, and comorbid mental health), criminal justice status, recent history and frequency of substance use, and recent SUD treatment history. This registry data will supplement information from the Medicaid data with additional socio-demographic and clinical information as well as SUD treatment that was not funded by Medicaid. Therefore, despite fragmentation in funding sources, the combination of these administrative data sets will yield a more inclusive record of treatment episodes. Through this targeted, innovative approach, we intend to identify the diverse treatment outcomes within this specific demographic across different program organizations and communities. The study has been reviewed by the Institutional Review Board of NYU Grossman School of Medicine (#s22-00914) and meets the criteria for exemption under 45 CFR 46.104(d). Study findings will be disseminated via national and international conferences, reports, and peer-reviewed publications.

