### Sample

The study cohort will be drawn from combined Medicaid and CDS data and will include approximately 65,000 individuals ages 18 to 25 whose first treatment episode for OUD in Medicaid occurs in 2012 or later—that is, not preceded by a prior OUD-related treatment episode in 2010 or later. Individuals who are co-insured with Medicare (some people under 65 with certain disabilities or conditions) will be excluded because not all their healthcare events are represented in the Medicaid claims data. We estimate that approximately 5,000 individuals will meet these criteria each year. Our link rate among all Medicaid enrollees with OUD ages 18–25 is 93%. The demographic and clinical profile is expected to be generally stable across years. Each year we will select TA adults receiving their first treatment for OUD. Once someone has joined a cohort, that person is retained in the analytical dataset in all future years. By using the first treatment episode in Medicaid as our index episode for a young cohort, we are identifying individuals early in their OUD treatment continuum of care. We estimate that about 26,000 TA adults will enter treatment after the COVID-19 public health emergency related telehealth and other measures take effect.

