## Status and timeline of the study

Access to both state treatment registry (CDS) and Medicaid claims has been acquired as of September 2023, but no data analysis has been done yet. Analysis is expected to start during the winter of 2023, after merging data from the two sources. Aim 1 analysis will begin during the winter of 2023, followed by Aims 2–3 concurrently. The study is set to be finished by the fall of 2025.

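### Aim 1 scores any MOUD during the episode for people who may enter right up to the end of the data, so late truncated episodes can lower observed MOUD use and appear as a post-COVID effect

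*Protocol article*

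**What the plan says.** The abstract describes "approximately 65,000 TA adults entering treatment for OUD between 2012 and 2025 in New York". The study design section describes a cohort built "using administrative data from 2010 through 2025". The Sample section sets yearly selection: "Each year we will select TA adults receiving their first treatment for OUD". It names no closing date for entry and no minimum observable time. On timing, the status section says: "The study is set to be finished by the fall of 2025".

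For Aim 1 the outcome is at episode level: "The primary outcome of interest is whether an individual received MOUD during the treatment episode". The model is a generalized linear mixed model for a binary outcome. Its time fixed effects are meant for secular trends, with the pre- and post-COVID periods as the example, and may be replaced by splines or power terms. A censoring assumption is stated under Aim 2, and Aim 3 follows the Aim 2 methods.

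The Analysis section announces a period comparison: "We also will compare pre- and post-COVID-19 treatment patterns". For the later period the Sample section says: "We estimate that about 26,000 TA adults will enter treatment after the COVID-19 public health emergency". The Discussion counts MOUD use among the outcomes to be examined against COVID-era changes in care.

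**The concern.** A binary any-time-in-episode outcome is fair across entry years only if every episode is observed to its close, or for the same length of time. With entry open until the data stop, the last entrants meet neither condition. Someone who would have started MOUD after the cut is recorded as never having started.

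The error has one direction: it can only remove MOUD starts. It also falls on one side of the COVID divide, because earlier entrants have years of later data. Time fixed effects cannot tell a shortfall caused by the cut from a real fall in MOUD use; they report both as a period effect. If splines or power terms replace them, the most truncated stretch becomes the end of the fitted trend. At stake is the reading of MOUD use after the telehealth and take-home changes: a spurious fall, or a real rise partly hidden.

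**Working it through.** **The plan's own figure.** Aim 1 claims 80% power for an odds ratio (OR) of 1.1 at 10% MOUD use, two-sided alpha 0.05, N above 65,000. OR 1.1 on a 10% base gives 0.1222/1.1222 = 10.89%. Comparing 10% with 10.89% needs 18,493 per group, 36,986 in all. With 65,000 people split 1:1 the power is 96.0%; with 20% exposed it is 84.7%, and with 15% exposed 76.1%. The claim holds for an exposed share of about 17% or more, before clustering. The power statement is not the error here.

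**Inputs from the article.** Entry is 5,000 a year and there are 26,000 post-COVID entrants (Sample), hence 26,000/5,000 = 5.2 years = 62.4 months of post-COVID entry and 65,000 − 26,000 = 39,000 earlier entrants. MOUD use is 10% (Aim 1 power statement) or 25% (the one-in-four background figure in the Introduction, which counts from diagnosis in other studies).

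**Assumptions.** Entry is uniform up to the data cut, there is no true change in MOUD use, and time from admission to start among those who would start is exponential with mean m months. The article gives no value for m, so I use 0.5 to 6 months.

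**Formulas.** For entrants over the last T months:
- share of starts lost L = (m/T)(1 − e^(−T/m))
- observed use q = p(1 − L)
- OR = [q/(1 − q)] / [p/(1 − p)]

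Example, m = 3, p = 10%:
- Whole post-COVID group, T = 62.4: L = 3/62.4 = 0.048, q = 9.52%, OR 0.947.
- Last entry year, T = 12: L = 0.25 × (1 − e^(−4)) = 0.245, q = 7.55%, OR 0.735.

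| Mean time to start | Post vs pre OR, 10% use | Post vs pre OR, 25% use | Last-year OR, 10% | Last-year OR, 25% |
|---|---|---|---|---|
| 0.5 month | 0.991 | 0.989 | 0.954 | 0.945 |
| 1 month | 0.982 | 0.979 | 0.908 | 0.892 |
| 3 months | 0.947 | 0.937 | 0.735 | 0.698 |
| 6 months | 0.894 | 0.876 | 0.542 | 0.496 |

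Starts spread evenly over 6 or 12 months (means 3 and 6) give the same whole-period ORs. The last-year ORs become 0.730 and 0.474 at 10% use, and 0.692 and 0.429 at 25%.

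**Chance of a falsely significant crude pre/post difference** (39,000 v 26,000, 10% use, nominal 5%, clustering ignored): 6%, 10%, 52% and 98% for means of 0.5, 1, 3 and 6 months.

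**If entry closes before the data do.** With 6 months between the last entry and the end of data, the whole-period OR is 0.99 to 1.00 for means up to 3 months, and 0.96 (10% use) or 0.95 (25%) at a mean of 6 months. With 12 months it is 0.98 or nearer to 1 in every case.

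**The case against.** **Entry up to the cut is not certain.** At 5,000 a year, 65,000 entrants is 13 years, which fits 2012 to 2024; entry through all of 2025 would give 70,000. The 14-year span in the Aim 3 power statement fits entry through 2025, but also 13 years of entry plus one of follow-up. Against this, the abstract puts entry itself as late as 2025. This stands as an ambiguity: the plain reading is entry into 2025, and the other reading removes most of the problem.

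**Starts may be quick.** Cohort members are already in treatment, and the article itself mentions early attrition; an episode that closes early loses nothing to the cut. This stands, and it is why the result is a range. A reader might infer that the whole post-COVID period will show falsely low use by about as much as the OR of 1.1 that the study aims to detect. The documents do not support that: it needs a mean start of about 6 months. At 1 month or less the whole-period effect is 1% to 2% in odds.

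**Claims lag.** A reader might enlarge the bias by assuming that the last months of claims are incomplete. The article mentions no lag. Since entry is defined by a Medicaid treatment episode, people whose entry claims are missing would largely not be in the cohort. I use no such figures.

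**Calendar time is mainly an adjustment term.** Aims 1a to 1c concern individual, community, program and medication-option factors, which the time effects largely protect. The period comparison is phrased around retention and outcomes, and no pooled pre/post OR for MOUD use is specified. The first part stands. But treatment patterns plainly include MOUD use, and the Discussion lists it among the outcomes to be set against COVID-era changes.

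**An article may leave details to a fuller plan.** True of a data-cut date or a run-out period. Here, though, the article itself fixes the entry years, the data years, the open-ended outcome and the binary model, and those choices conflict. Monthly measurement and the time-varying label in Table 1 do not resolve this, because the named primary outcome is per episode.

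**Conclusion.** The point holds in limited form. As written, the Aim 1 outcome can understate MOUD use among the latest entrants, and the model would show the shortfall as a post-COVID period effect. The direction is fixed; the size is not.

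Under entry at 5,000 a year to the data cut and no true change, the post- versus pre-COVID OR is about 0.98 to 0.99 for mean starts of 0.5 to 1 month, 0.94 to 0.95 at 3 months and 0.88 to 0.89 at 6 months. For the last entry year it is 0.89 to 0.95, 0.70 to 0.73 and 0.50 to 0.54. All of this rests on an assumed time to first MOUD. If entry closes in 2024 the bias is close to nil. The other Aim 1 associations are largely safe. The point deserves correction because the bias runs one way, touches a planned comparison and is cheap to remove.

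**What to change.** - State the last entry date and the last complete claims month.
- In Aim 1, limit the MOUD-use model, and any pre/post-COVID comparison of MOUD use, to episodes that start at least a fixed period before that month. Six months is an example, not a required value.
- For the pre/post contrast, count MOUD only within that same window after admission in every year, at least as a sensitivity analysis beside the any-time-in-episode outcome. The restriction alone is not enough if starts are slow (OR still 0.95 to 0.96 at a mean of 6 months); with an equal window, bias from unequal observation time is zero.
- Keep later entrants in the censored time-to-event analyses.

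Cost with 6 months: about 2,500 of 65,000 entrants (3.8%) leave the Aim 1 analysis. Power for OR 1.1 at 10% use falls from 96.0% to 95.4% at 1:1 exposure, from 84.7% to 83.3% with 20% exposed, and from 95.4% to 94.2% for the pre/post contrast (39,000 v 23,500). The fixed-window result also answers a slightly different question, MOUD within the window rather than at any time in the episode, and should be labelled so.
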